### Healthcare delivery: Intervention group and control group

Frail older persons in the intervention group receive the proactive, integrated care approach FFF as was previously described in detail. Frail older people in the control group receive usual care services available for older people as arranged by their GP practice and local health and community organizations.

### Data collection and informed consent for the evaluation study

Older persons in the intervention group and control group are interviewed at home at baseline (T0) and 12 months thereafter (T1). Interviewers are recruited in the western part of the Province of North Brabant in the Netherlands to assure a cultural fit with the older persons and all interviewers have a background in healthcare. Interviewers are trained to conduct the interviews and are blinded to the status of the older patients, i.e. patient of an intervention GP practice or control GP practice. Before contacting potential eligible older persons to participate in the study, the GP assesses whether reasonable grounds to suspect incapacity to either participate in the study or to give consent due to cognitive impairment exist (based on their medical records and latest encounters with the GP). In case of doubt the GP will contact the older person’s informal caregiver (spouse or children) to discuss the patient’s current (cognitive) state which will lead to the GP’s final assessment. Those who are considered incapable by the GP will be excluded from the study. This procedure will be followed at both T0 and T1. Eligible older patients are then informed by telephone and during the home visit about the study (verbal explanation of the study purposes, procedures, confidentiality, and contact information). In addition, patients receive a leaflet with research information. It is explicitly stated to patients that their voluntary participation in the evaluation study does not affect healthcare delivery. Patients registered at intervention GP practices can participate in the FFF approach even though they are not willing to participate in the evaluation study. Patients that are willing to participate in the evaluation study are interviewed after they sign an informed consent form. The informed consent form states that the patient may discontinue participation in the study at any time without adverse consequences or loss of benefits. On average, the duration of an interview is 60-75 minutes. Outcome data and demographic data from healthcare professionals are also collected at baseline (T0) and 12 months thereafter (T1) (see section ‘Outcome measures and measurement instruments’). Postal self-report questionnaires are used to collect data among the professionals involved in the healthcare delivery for frail independently living older patients. After 2-3 weeks, reminders are send to non-responders by mail and/or healthcare professionals are reminded by means of a telephone call.

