Process indicators are registered continually during the follow-up period of 12 months. Descriptions of patient visits by practice nurses and geriatric nurses, medication reviews, assessment outcomes, and individualized care plans describing the provided self-management support are analyzed. Data are collected from data registries (e.g. information systems). We collect data on several process indicators that are specifically related to the FFF approach. Examples are the number of frail older patients that are discussed in multidisciplinary consultations, the number of older adults that have an individualized care plan, and the number of multidisciplinary consultations per year. Moreover, field notes are made at several multidisciplinary consultations executed by intervention GP practices and general meetings related to the FFF approach. Examples are educational meetings for geriatric nurses and practice nurses, steering committees, and working groups. Furthermore, semi-structured face-to-face interviews are conducted with a sample of healthcare professionals involved in the care process for frail independently living older patients. We aim to interview a diverse group of professionals, including practice nurses, elderly care physicians, and case managers. Hence a purposeful sampling procedure will be used, which can be used in qualitative research to collect data from the participants who are knowledgeable about the topic [114, 115]. Healthcare professionals are encouraged to describe and reflect on their experiences with healthcare delivery for frail older patients living in the community. In addition, several professionals involved in the management of healthcare delivery are interviewed. Examples are the project manager of the FFF approach and policy advisors of different healthcare organizations (e.g. homecare agencies). Also, semi-structured face-to-face interviews are held with a sample of independently living frail older persons. The aim is to gather the reflections on experiences of patients with the FFF approach (intervention group) or care as usual (control group) from their own perspective. To create a diverse sample of older people, we aim to select participants with different characteristics. Besides these semi-structured interviews, face-to-face interviews based on a more structured interview template are held with GPs of all participating GP practices as well. As the GP has the lead in the implementation and execution of the FFF integrated care approach, we decided to interview GPs to assess exactly how care is being delivered in the different intervention GP practices. We also assess how care for community-dwelling older people is being delivered in the control GP practices (care as usual). We developed an interview template based on the Chronic Care Model (CCM) [38, 97]. The CCM highlights system changes in several areas (e.g. decision support and clinical information systems) to guide quality improvements [38, 97]. Important interventions related to care delivery are classified according to the areas of system change in the interview format. Examples of interventions are the systematic follow-up of patients and the use of clinical guidelines. Data about the implementation of these various interventions within each of the areas of system redesign are collected. Altogether an extensive description of (un)successfully implemented interventions is provided. Interviews are recorded with permission of the GPs and finalized data are send back for member checking and corrections.

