### Sample size

We aim to include 500 frail older patients (250 patients of intervention GP practices and 250 patients of control GP practices). We aim to optimize participation by means of personal home visits, however, we anticipate a drop-out rate of approximately 20% between T0 and T1 (e.g. due to death, refusal). Accordingly, we expect 400 patients at T1 in the intervention and control groups. Sample size calculations are based on the mean well-being score (SPF-IL) of a comparable Dutch population of frail community-dwelling older persons (N=945) [137]. To detect a mean improvement in well-being of 1/4 standard deviation (SD) based on the SPF-IL, we need at least 198 older patients in each group (based on a mean SPF-IL score of 2.56 [SD = 0.45]; alpha (two-sided) = 0.05, beta = 0.20, ratio 1:1).

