### Statistical analyses

Descriptive statistics are used to describe the study population at the two time points in the evaluation study (baseline and 12 month follow-up). Baseline variables are compared to detect differences between patients and professionals in the intervention group (FFF approach) and control group (care as usual). To assess baseline differences between the groups we use unpaired Student’s t-tests (continuous variables with normal distributions), Mann-Whitney U-tests (continuous variables with non-normal distributions) and Chi-square tests (categorical variables). Effect analyses are performed based on the intention-to-treat principle. Analyses of outcomes are performed by means of univariate, multivariate, and multilevel methods (to account for the nested structure of the data). To analyze the differences in outcomes between the intervention group and control group, we employ linear mixed model with random effects (multilevel analysis). To estimate the effects of the FFF approach after 12 months a difference in differences model will be used followed by a sensitivity analysis method specifically developed for difference in differences model based on more general methods of bounds developed by Rosenbaum [138]. Potential confounding and effect modification is accounted for when performing the analyses and, if necessary, adjustments for baseline differences are made. To handle missing data multiple imputation techniques will be used. Ultimate goals of these analyses are to test the assumptions of the theoretical framework with the instruments described in the study protocol. Finally, we will assess clinical relevance of improvements made in cognitions and behaviors among both patients and professionals. The software package IBM SPSS statistics version 23 is used for all statistical analyses.

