The proposed evaluation study has potential limitations and challenges. First, the absence of randomization makes the design more susceptible to bias [139]. Especially selection bias is a major concern in non-randomized studies. Systematic differences between the groups result in incomparable groups which ultimately may lead to biased estimates of the intervention effect [140]. To reduce the impact of this bias on the outcome measures studied, we aim to control for important factors in the analysis of the data and by means of matching [141]. To ensure that the intervention and control groups are similar for key covariables, we use one-to-one matching to balance groups instead of matching on a higher level (at healthcare practice level). Moreover, when necessary we use case-mix adjustments to take into account important dissimilarities. However, it is stated by Deeks and colleagues [140] that the degree to which techniques can sufficiently adjust for differences between the groups is still unclear, which ultimately provides no guarantee for unbiased study results [140]. In addition, unknown and unmeasured factors can still influence the outcome [142]. Second, the design of the study makes it impossible to blind participating healthcare professionals and frail older patients. Knowledge of the status of the person (receiving either the FFF approach or care as usual) may have an influence on the responses and may affect compliance [143]. Nevertheless, the interviewers that conduct the interviews with frail older persons are kept unaware of the group the person is in (intervention or control GP practice), so that the interviewers collecting outcome data are not influenced by that knowledge. Blinding of the interviewers aids to reduce differential outcome measurements (information bias) [143]. Due to the nature of the evaluation study, however, it is possible that the patient inadvertently reveals his or her status during the interview (e.g. disclosing information that is specific to the FFF approach). Third, one of the core challenges of the evaluation study is the willingness of frail community-dwelling older patients to participate in the study, especially in the long-term. Recruitment of appropriate numbers of patients requires a sufficiently long period [144]. We aim to optimize participation in the evaluation study by means of home visits instead of interviews over the telephone, recruiting interviewers that live in the same region as the older adults, and sending letters to older patients on behalf of their own GP. Fourth, although control GP practices continue to provide usual care, GPs in the control group may start initiatives to improve care delivery for frail older patients. We collect data on various interventions that are implemented to improve care for older adults and we monitor and describe the activities performed by the GPs. In contrast to the intervention GP practices, control practices are not supported financially by the health insurers to implement elements of the FFF approach. Fifth, recall bias may potentially affect our study findings. Earlier research using a 12 months period of asking patients about their healthcare visits show both under-reporting and over-reporting effects [145]. Administrative data could be included to accurately capture resources for an economic evaluation (if filled in correctly). Sixth, while we included patients and professionals in our theoretical framework and study protocol we did not include informal caregivers. Given their important role in supporting community-dwelling frail older people they are expected to influence the well-being of older persons as well. Given the complexity of the theoretical framework as presented in this paper we decided to first unravel the underlying mechanisms in the relationship between quality of care, cognitions and behaviors of patients and professionals and older persons’ well-being. Future research should look at the role of informal caregivers and their cognitions and behaviors as well. It may be easier to improve outcomes if the patient’s partner is a good self-manager with a positive frame of mind compared to a partner who is depressed, has low self-efficacy and poor investment behavior.

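### Patients their unblinded GP judges incapable at T1 are to be excluded from the study, and the plan does not reconcile this with intention-to-treat and multiple imputation

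*Protocol article*

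**What the plan says.** Data collection and informed consent for the evaluation study: before patients are contacted, the GP assesses whether cognitive impairment may make them unable to take part or to consent. The assessment is "based on their medical records and latest encounters with the GP", and in case of doubt the GP consults the informal caregiver. Then: "Those who are considered incapable by the GP will be excluded from the study. This procedure will be followed at both T0 and T1".

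Statistical analyses: "Effect analyses are performed based on the intention-to-treat principle". The only missing-data rule is "To handle missing data multiple imputation techniques will be used". The 12-month effect is to be estimated with a difference-in-differences model.

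Strengths and limitations: "the design of the study makes it impossible to blind participating healthcare professionals and frail older patients". Only the interviewers are blinded. Process evaluation: "As the GP has the lead in the implementation and execution of the FFF integrated care approach", GPs are interviewed on how care is delivered.

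Sample size: about 20% drop-out between T0 and T1 is expected, with death and refusal given as examples. T1 incapacity is not mentioned.

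**The concern.** A capacity check at entry defines who is studied. The same check a year later selects on something that happened during follow-up, which the care under study might itself affect. Cognitive decline is a likely determinant of well-being, so those lost this way are unlikely to resemble those who stay. Each removal also leaves a one-to-one matched partner without its pair.

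The person deciding knows the group, and the information behind the decision differs by design. In FFF practices, nurses and case managers make home visits, an MMSE may be done when needed, and every case goes to multidisciplinary consultation (Proactive case finding; Case management; Multidisciplinary teams). Control practices were eligible only if they were not engaged in or planning frailty screening and did not already follow up older persons systematically (Setting and GP practices). The same degree of decline could therefore be recorded more often in one group than in the other. A difference-in-differences model does not in general remove selection that occurs after baseline.

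**Working it through.** **The plan's own figure.** 500 × (1 − 0.20) = 400, which agrees with "we expect 400 patients at T1 in the intervention and control groups". No stated figure gives the share expected to be judged incapable at T1, so what follows is illustration.

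**Two readings of the T1 rule.**

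1. *Removed from the analysis set.* Enrolled patients are dropped for a post-baseline reason. This conflicts with intention-to-treat, and multiple imputation never reaches them.
2. *Not interviewed, T0 data kept, T1 imputed.* This is compatible with the Statistical analyses section, but it is written nowhere. Imputation that assumes data are missing at random would still not cover loss caused by decline after T0 that the T0 variables do not predict.

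**Size under reading 1, comparing T1 levels.**

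Inputs from Sample size: SD 0.45; target 1/4 SD = 0.25 × 0.45 = 0.1125 points.

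Assumed: share excluded pI (FFF) and pC (control); gap g by which excluded patients lie below retained patients in the same group.

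Excluding a share p raises a group's observed mean by p × g. With the same g in both groups, the shift in the contrast is (pI − pC) × g, in favour of the group with more exclusions.

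| Excluded, FFF vs control | g = 0.5 SD | g = 1 SD | Share of 0.25 SD target |
|---|---|---|---|
| 10% vs 10% | 0 | 0 | 0% |
| 8% vs 4% | 0.020 SD | 0.040 SD | 8–16% |
| 10% vs 5% | 0.025 SD | 0.050 SD | 10–20% |
| 15% vs 5% | 0.050 SD | 0.100 SD | 20–40% |

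In SPF-IL points, the 10% versus 5% row is 0.025 × 0.45 = 0.011 to 0.05 × 0.45 = 0.023. The signs reverse if controls are excluded more often.

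Equal rates alone do not guarantee zero. At 10% in each group, with gaps that differ by 0.5 SD, the shift is 0.10 × 0.5 = 0.05 SD, or 20% of the target.

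**Size for the planned estimator.** If an excluded patient's T0 value leaves as well, what matters in a difference-in-differences model is the gap in change: g at T1 minus g at T0. A patient 1 SD low at T1 who was already 0.5 SD low at T0 contributes 0.5 SD. At 10% versus 5% the shift is then 0.05 × 0.5 = 0.025 SD (10%), not 0.05 SD. If the two gaps are equal, the shift is zero.

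**Size under reading 2.** The same formula applies, but g is only the part of the T1 gap that the imputation model fails to predict.

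**The case against.** The sentence stands in a section on contact and consent, not on analysis sets. Not interviewing someone who cannot consent is a proper safeguard. Read that way, the patient stays in the intention-to-treat population and T1 is imputed, which is what the Statistical analyses section implies. A reader might infer that the plan plainly breaches intention-to-treat. The documents do not support that, because none of the text says these patients leave the analysis set. But the words used are exclusion from the study, and nothing limits them to the interview, so two sections remain to be reconciled.

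A reader might also infer that bias will favour FFF. The procedure is the same in both groups, and all participating GPs receive the TFI scores. The extra home visits are made by nurses and case managers rather than by the GP. If FFF slowed decline, exclusions could be higher among controls. That objection stands as far as direction goes. It does not remove the difference in information or the lack of blinding.

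Finally, because death is an example of drop-out and imputation is the only missing-data rule, a reader might infer that well-being and utilities will be imputed for people who have died. The article does not say so. The example concerns how many patients remain at T1, and Economic evaluation defines QALYs as including length of life. How deaths enter the QALY calculation is at most a point to clarify in the full plan.

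**Conclusion.** The point holds as an unreconciled conflict between the T1 exclusion rule and the analysis principles. It is not a demonstrated breach or a demonstrated bias. The T1 rule, the unblinded decision-maker and the unequal information base are all in the text. That decline is related to well-being, and is noticed more readily in one group, is plausible but not shown.

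The 10 to 20% of the target effect for 10% versus 5% rests wholly on assumed rates and gaps. It describes a comparison of T1 levels after removal. Under the planned difference-in-differences analysis, or with good imputation, the effect may be smaller, and with equal rates and gaps it is zero. The change is worth making because it is cheap and removes a choice that could otherwise be settled after the data are seen.

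**What to change.** - Use the GP's capacity judgement as an exclusion from the study at T0 only. At T1 it decides only whether an interview is held, so the safeguard stays.
- Keep patients judged incapable at T1 in the analysis set with their T0 data. Record T1 SPF-IL and EQ-5D as missing with the reason incapacity.
- Impute these values using T0 SPF-IL, MMSE-12, Katz ADL, TFI and practice, all of which the study already collects or knows.
- Report the number judged incapable at T1 by group.
- Add a sensitivity analysis in which imputed values for these patients are set lower, for example by 0.5 to 1 SD, and state whether the conclusion changes.

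Cost: a few sentences in the protocol and analysis plan and one extra analysis, with no added visits. The small downside is that more values are imputed.

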
### Outcome measures and measurement instruments

To assess the effectiveness of the FFF integrated primary care approach in improving well-being of frail community-living older patients, we selected measurement instruments that are particularly relevant for measuring all the concepts incorporated in our proposed theoretical model. All outcomes are measured at baseline (T0) and 12 months thereafter (T1). Outcome measures for the economic evaluation are described in the section ‘Economic evaluation’.

### Primary outcome measure

#### Well-being

To measure individuals’ realization of universal goals needed to enhance their well-being, the 15-item Social Production Function Instrument for the Level of well-being (SPF-IL) is used [34]. Social Production Function (SPF) theory, as introduced by Lindenberg [52–54], asserts that five instrumental goals, i.e. comfort, stimulation, status, behavioral confirmation, and affection, are important for optimizing the universal goals of physical and social well-being [32, 33]. This instrument has been thoroughly validated by Nieboer and colleagues [34] and is used frequently among (frail) older populations (e.g. [44, 51]).

### Secondary outcome measures

#### Cognitive and behavioral components

##### Productive patient-professional interaction

To assess productive patient-professional interactions, we measure dimensions of communication and relationships among community-living frail older persons and their healthcare professionals using a validated relational coproduction instrument. Relational coproduction will be measured by means of 7 survey questions. Frequency, timeliness, accuracy, and problem-solving nature of communication as well as quality of the relationships are measured. The latter aspect focuses on mutual respect and the extent to which goals and knowledge are shared. Frail older patients are asked to assess the quality of their communication and relationships with the healthcare professionals involved in their care process (e.g. GPs, practice nurses, physiotherapists). Similarly, healthcare professionals assess the quality of the communication and relationships with patients. Together these dimensions form the relational coproduction construct [76, 91–93].

##### Cognitions and behaviors of frail older people

Cognitive and behavioral self-management abilities are measured by means of the short version of the Self-Management Ability Scale (SMAS-S). The SMAS-S contains 18 items assessing six core cognitive and behavioral abilities of self-management, i.e. self-efficacy beliefs, a positive frame of mind, taking initiative, investment behavior, multifunctionality of resources, and variety in resources [57, 60, 94]. This instrument has also been thoroughly validated among older populations by Cramm and colleagues [94].

